## Methods

### Study setting and design overview

This study will be conducted at the Kyung Hee University Korean Medicine Hospital in Seoul, Korea. The study is designed as a randomized, double-blind, placebo-controlled, single-center, phase IIa clinical trial to investigate the safety, preliminary efficacy, and dose response of *Jaungo* for treatment of AD. The study aims to enroll 34 patients with AD. Participants fulfilling the eligibility criteria will be selected and randomly distributed into three parallel groups: treatment 1, treatment 2, and the placebo group. Treatment group 1 applies *Jaungo* twice a day; treatment group 2 applies *Jaungo* and placebo ointments once a day, separately; and the placebo group applies placebo ointment twice a day, for a total of 3 weeks each. Participants will be evaluated for AD before and after applying ointment (see Figs. 1 and 2). A completed Standard Protocol Items: Recommendations for Interventional Trials (SPIRIT) Checklist for the trial is available (see Additional file 1).

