### Statistical analysis

The primary hypothesis is that topical application of *Jaungo* is more effective than the placebo ointment for treating AD. Baseline data collected on each participant at randomization in the trial will be used to describe the population of patients, assess comparability of treatment groups, achieve balanced randomization, adjust for possible confounding prognostic factors, and undertake subgroup analyses. The baseline characteristics of the three groups, including sex, age, duration of AD, total IgE level, and SCORAD score will be compared. Analysis of variance (ANOVA) will be used to investigate differences in continuously scaled variables, and chi-squared tests will be used to identify significant variations in proportions across treatment groups.

We will also compare the efficacy of *Jaungo* and placebo ointments based on the change in primary outcome, or EASI score, from day 0 to the end of the study period (3 weeks). Mean differences in the EASI score from baseline value to the end of treatment will be compared using ANOVA among the three groups. A paired Student’s *t* test will be used to compare the mean change within a group. Secondary outcomes (SCORAD score, TEWL, DLQI, total IgE, eosinophil count, IL-17, IL-22, and IFN-γ) will also be utilized to compare the efficacy of *Jaungo* and placebo ointments in the same manner as the primary outcome/EASI score. To evaluate safety, the Draize score and adverse events will be presented in a descriptive manner.

Analyses will be performed for two populations: (1) an intention-to-treat population consisting of all randomized participants who have at least one measurable outcome to report following treatment (missing data are replaced with the last observation values) and (2) a per-protocol population including only participants without major protocol deviations. All data will be descriptively analyzed. All main analyses will be based on the intention-to-treat population and conducted using the last observation carried forward imputation method. Statistical analyses will be conducted in a blind manner by an independent statistician and performed using the SPSS 21 (IBM Inc., Armonk, NY, USA), where the level of significance is established at *α* = 0.05.

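### The EASI tests fixed in the protocol, a three-group ANOVA and within-group paired t tests, do not test its hypothesis that Jaungo beats placebo or its dose-response aim

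*Protocol article*

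**What the plan says.** The Statistical analysis section of the protocol article opens with a directional statement: "The primary hypothesis is that topical application of *Jaungo* is more effective than the placebo ointment for treating AD". It does not say which Jaungo regimen the hypothesis refers to. The Study setting and design overview gives the aim as to "investigate the safety, preliminary efficacy, and dose response of *Jaungo* for treatment of AD". Dose response is named again in the Abstract, the Background, the Sample size section and the Discussion. The arms are ordered by exposure: "Treatment group 1 applies *Jaungo* twice a day; treatment group 2 applies *Jaungo* and placebo ointments once a day, separately", with a third group on placebo only. That is 2, 1 and 0 Jaungo applications a day.

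For the primary outcome the section says it will compare the efficacy of Jaungo and placebo, and then names two tests. Between groups: "Mean differences in the EASI score from baseline value to the end of treatment will be compared using ANOVA among the three groups". Within groups: "A paired Student’s *t* test will be used to compare the mean change within a group". The secondary outcomes are handled the same way. Alpha is 0.05, with sidedness not given. No contrast, trend test or comparison of an individual arm with placebo is named.

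**The concern.** The tests do not match the question. A significant three-group F test says that the means are not all equal. It does not say that Jaungo is better, which regimen is better, or whether more applications do more. It can reject because the two Jaungo arms differ from each other, or because Jaungo is worse. The plan then fixes no further step that turns the result into a statement about Jaungo against placebo.

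The paired t test cannot fill the gap. It combines any drug effect with the effect of the ointment base, regression to the mean and permitted co-treatment. That matters here because the placebo is itself an oil-and-wax ointment and emollients are allowed in every arm, so improvement on placebo is plausible.

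An analysis plan that carried out this section faithfully would inherit the mismatch. If the comparison were instead chosen after unblinding, it would be post hoc.

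**Working it through.** **Inputs.** From the protocol: 34 participants randomized 1:1:1 with 11–12 per group (Randomization and allocation), and alpha 0.05 (Statistical analysis). I used 12 placebo, 11 once daily and 11 twice daily, with two-sided tests. The Sample size section gives 12 per group, which would be 36; with 12 in each group the omnibus and linear-contrast powers below rise by only about 2 to 4 points. The document states no power, effect size or SD, so there is no figure of its own to reproduce. Effects are assumed, in SD of EASI change, and written as (placebo, once daily, twice daily).

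**1. What the omnibus test can detect.** Power comes from the noncentral F on 2 and 31 df, with noncentrality λ = Σ nᵢ(μᵢ − μ̄)².
- No average benefit, (0, −0.5, +0.5): μ̄ = 0 and λ = 11 × 0.25 + 11 × 0.25 = 5.5, giving power 50%.
- No effect anywhere: in 100,000 simulated trials it rejected in 5.0%, and in 2.4% it did so with the Jaungo arms on average no better than placebo. About half of its false positives therefore point the wrong way.

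**2. Paired t tests with no drug effect.** Let every arm improve by the same δ SD of change. Each arm's power is a one-sample noncentral t with noncentrality δ√n. The misleading pattern is placebo non-significant with at least one Jaungo arm significant: P = (1 − p₁₂)[1 − (1 − p₁₁)²], where p₁₂ and p₁₁ are the powers at n = 12 and n = 11.
- At δ = 0.5: p₁₂ = 0.353 and p₁₁ = 0.323, so P = 0.647 × (1 − 0.677²) = 0.647 × 0.542 = 35%.

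| Equal improvement in all arms (SD of change) | 0.3 | 0.5 | 0.7 | 0.8 | 1.0 | 1.2 |
|---|---|---|---|---|---|---|
| P(misleading pattern) | 23% | 35% | 32% | 25% | 11% | 3% |

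**3. Alternatives, at a maximum effect of 1.0 SD.**
- Omnibus, linear shape: μ̄ = 16.5/34 = 0.485 and λ = 12 × 0.485² + 11 × 0.015² + 11 × 0.515² ≈ 5.74, giving 52%.
- Linear contrast (−1, 0, +1): noncentrality = 1.0/√(1/12 + 1/11) = 2.40 on 31 df, giving 64%. The once-daily mean has zero weight, so this is twice daily against placebo with a pooled variance.
- Pooled contrast (−1, ½, ½): both Jaungo arms together against placebo.
- Dunnett, each Jaungo arm against placebo: correlation (1/12)/(1/12 + 1/11) = 0.48 and two-sided critical value about 2.32 by simulation. Power is the chance that at least one arm is significant.

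| True shape | Omnibus | Dunnett | Linear contrast | Pooled contrast |
|---|---|---|---|---|
| Linear (0, 0.5, 1) | 52% | 56% | 64% | 53% |
| Plateau (0, 1, 1) | 66% | 70% | 64% | 77% |
| Twice daily only (0, 0, 1) | 64% | 55% | 64% | 27% |
| Once daily only (0, 1, 0) | 64% | 55% | 5% | 27% |
| Once daily better (0, 1, 0.5) | 52% | 56% | 21% | 53% |

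Under the linear shape, omnibus against linear contrast is 16% v 21% at 0.5 SD, 35% v 46% at 0.8 SD and 69% v 80% at 1.2 SD.

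**The case against.** The strongest defence is that this is a condensed article on a phase IIa study that calls itself preliminary and exploratory, with a size set largely on feasibility. Follow-up comparisons after an ANOVA are often left to the analysis plan, and the omnibus test makes no assumption about the shape of the response. The Discussion says that nothing is known about dose or frequency in AD, so neutrality about shape has value. These points limit how much weight the finding carries. They do not remove it: the section sets a primary hypothesis and an alpha, and selects a test that does not address that hypothesis.

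Three stronger readings are tempting, and the document does not support them.
- **That one planned contrast would answer both questions with more power.** The linear contrast gains only when the response is roughly linear. It cannot tell a graded response from a plateau or from a twice-daily-only effect (64% in all three), and it falls to 5–21% if once daily is the better arm. The pooled contrast has the opposite weakness and says nothing about dose.
- **That the paired t test is a primary test.** The protocol does not call it that.
- **That efficacy will be claimed from a significant result on Jaungo beside a non-significant one on placebo.** The protocol announces no such reading. The percentages in step 2 measure a hazard, and it shrinks when the common improvement is large.

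**Conclusion.** The concern holds as a mismatch between question and test. The hypothesis is that Jaungo "is more effective than the placebo ointment for treating AD" and dose response is an aim, but the one between-group test fixed for EASI and the secondary outcomes is non-directional, blind to dose order and not a comparison with placebo. The within-group tests have no control. They would produce a pattern resembling efficacy in 23–35% of trials with no drug effect if all arms improved by 0.3 to 0.8 SD of change, and in 11% and 3% at 1.0 and 1.2 SD.

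No general loss or gain of power should be asserted. Every power figure rests on assumed standardized effects, normal data, equal variances and 12/11/11 with no dropout, and the ranking of the tests changes with the true shape.

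**What to change.** Before unblinding:
1. State that the primary hypothesis is tested by comparing each Jaungo arm with placebo on week-3 EASI change, Dunnett-adjusted at 0.05 with sidedness stated. Give both differences with 95% CIs. This replaces the omnibus ANOVA in that role.
2. Add a pre-specified linear trend over 0, 1 and 2 Jaungo applications a day as a secondary dose-response analysis. Read it together with the once-daily estimate, because the trend contrast gives that arm zero weight.
3. Report within-group mean change descriptively, without p values.
4. Carry the same structure to the secondary outcomes.

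The cost is analysis wording only; data, sample size, conduct and blinding are unchanged. The price in power, at a maximum effect of 1.0 SD, is about 55% v 64% for the omnibus test if only one Jaungo arm works. Against that stand 56% v 52% under a linear response and 70% v 66% under a plateau. The reason to change is that the result would answer the stated question.

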### Intervention discontinuation

Participants may discontinue the trial in the following cases: violation of the inclusion/exclusion criteria, violation of combinational medications, the occurrence of serious adverse events, request by participant due to side effects, determination by the investigator due to side effects, systematic disease discovered during the trial, request of participant or their guardian to discontinue, the need for surgery or hospitalization due to accidents or diseases, pregnancy, worsening of atopic dermatitis, continuation judged inappropriate by the investigator.

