### Early closure

If participant AD symptoms disappear, the investigator may terminate the case early after discussion with the sponsors and the statistician.

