## Outcomes

### Primary outcome measurement

The primary outcome will be measured by changes in the Eczema Area and Severity Index (EASI) before and after 3 weeks’ application of experimental medications. Key signs of eczema, including erythema (E), infiltration/population (I), excoriation (Ex), and lichenification (L), will be assessed on a numeric scale of 0 to 3. Then, the percentage of area involved for each of the four body regions will be assigned a proportional score from 0 to 6: 0 = no eruption; 1 = <10%; 2 = <10–29%; 3 = <30–49%; 4 = <50–69%; 5 = <70–89%; and 6 = >90–100%. Finally, an established multiplier based on the age of the patient will be used. Please refer to the following formula for patients over 8 years of age. The multiplier for patients under 8 years of age is indicated in parentheses and in italics:

Upper Limbs [(E + I + Ex + L) × Area × 0.2 (*0.2*)] + Lower Limbs [(E + I + Ex + L) × Area × 0.4 (*0.3*)] + Trunk Limbs [(E + I + Ex + L) × Area × 0.3 (*0.3*)] + Head/Neck [(E + I + Ex + L) × Area × 0.1 (*0.2*)] [11].

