### Secondary outcome measurements

Secondary outcome measurements will include SCORAD score [12], transepidermal water loss (TEWL) using TM 300 [13], the Dermatology Life Quality Index (DLQI) [14], total IgE, eosinophil count, and interleukin (IL)-17, IL-22, and interferon (IFN)-γ [15]. These parameters will be measured before and after 3 weeks’ application of experimental medications. The consumption of orally administered antihistamines and usage of emollients, lotions, and ointments that do not contain GCs during the study will be checked.

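### Last observation carried forward has no planned on-treatment EASI to carry, and the intention-to-treat set can lose early leavers, so the main analysis may not preserve the randomised comparison

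*Protocol article*

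**What the plan says.** All references are to the protocol article.

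- **Primary outcome measurement:** the endpoint is "changes in the Eczema Area and Severity Index (EASI) before and after 3 weeks’ application of experimental medications". The Statistical analysis section uses the same two points, day 0 and 3 weeks.
- **Secondary outcome measurements:** "These parameters will be measured before and after 3 weeks’ application of experimental medications".
- **Visits:** randomisation is at the second visit (Randomization and allocation) and containers are counted at visit 3 (Adherence assessment). The text names no visit between them.
- **Analysis set:** "an intention-to-treat population consisting of all randomized participants who have at least one measurable outcome to report following treatment".
- **Missing data:** "All main analyses will be based on the intention-to-treat population and conducted using the last observation carried forward imputation method".
- **Ways out of the trial:** Intervention discontinuation lists side effects and "worsening of atopic dermatitis", among other reasons. Combination medications removes participants who received drugs that may affect AD. Early closure adds: "If participant AD symptoms disappear, the investigator may terminate the case early after discussion with the sponsors and the statistician".

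None of the three sections on leaving links an EASI assessment, at exit or at week 3, to the event.

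**The concern.** LOCF needs an earlier post-baseline value to carry, and the described schedule supplies none. The set definition also requires a post-treatment outcome, so a person who leaves before the only planned post-baseline assessment can fall out of the analysis that is called intention-to-treat.

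This matters because several routes out are related to the outcome: worsening disease, side effects, use of other AD medication, and clearance. If losses differ between arms and depend on response, the arms being compared are no longer those that randomisation created, and the stated missing-data rule does not repair that. With 11 to 12 participants per arm, each loss is 8% to 9% of an arm (1/12 = 8.3%, 1/11 = 9.1%).

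**Working it through.** **1. Apply the stated rules to each kind of participant.**

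| Participant | In the main set? | What LOCF does to EASI |
|---|---|---|
| Week-3 EASI present | Yes | Nothing; no value is missing |
| No post-treatment outcome at all | No | Nothing; the person is not analysed |
| Another post-treatment outcome, EASI missing | Yes; the definition does not name EASI | Carries baseline: change = 0 |
| Left early, unscheduled EASI taken at exit | Yes | Carries the exit score as the week-3 result |

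Only the last two rows give LOCF any work. The third carries baseline. The fourth depends on a measurement that the text does not plan. In no row does LOCF carry a planned on-treatment EASI.

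**2. How many might be lost.** The article gives no dropout rate, so these rates are assumptions. With loss fraction f, participants analysed = 34 × (1 − f):

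- 5%: 32.3
- 10%: 30.6
- 20%: 27.2
- 30%: 23.8

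**3. Illustrative bias.** Assumptions: no true effect; change in EASI normal with the same SD in each arm; higher change means worse; 12 per arm; the participants lost are exactly the worst responders. Removing the k worst of n moves the mean of those remaining by −(sum of the k largest expected normal order statistics)/(n − k). For n = 12 the three largest are 1.629, 1.116 and 0.793 SD.

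- Placebo loses 3: −(1.629 + 1.116 + 0.793)/9 = −3.538/9 = −0.393 SD.
- Jaungo loses 1: −1.629/11 = −0.148 SD.
- Shift in the arm difference: 0.393 − 0.148 = 0.245, about 0.25 SD. Placebo looks better, so the bias is **against** Jaungo.
- Standard error with 9 and 11 left: √(1/9 + 1/11) = 0.449, about 0.45 SD.
- Ratio: 0.245/0.449 = 0.55 of a standard error.

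With 4 placebo losses instead of 3, the fourth order statistic (0.537) is added: (3.538 + 0.537)/8 = 0.509, and 0.509 − 0.148 = 0.361 SD. The standard error is √(1/8 + 1/11) = 0.465 SD, a ratio of 0.78.

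By symmetry, swapping the arms gives the same shifts **toward** Jaungo.

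**The case against.** **Asymmetric handling.** A reader might infer that participants who worsen are deleted while those who clear are locked in at their best score. The documents do not support this. Intervention discontinuation and Early closure are equally silent on an exit assessment. If an exit EASI is taken, a worsener stays in the set with the bad score carried; if none is taken, a participant who cleared drops out too.

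**A pure completers set.** Calling the main set a completers set, or saying that LOCF never acts, is also too strong. The definition asks for any measurable outcome, so someone with, say, a DLQI but no EASI remains with change 0, and an exit score would keep an early leaver in. Neither route supplies a planned on-treatment EASI, so the mismatch remains.

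**Missing schedule figure.** Fig. 2 is not shown, and the article condenses a fuller protocol, so an interim or exit EASI cannot be ruled out. This limits certainty. However, the article itself states the set, the imputation rule and the measurement times, and as stated they do not work together. That is different from leaving detail to another document.

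**Size and direction.** The losses in the illustration are invented, the bias shown is below one standard error, and its direction would make a false positive for Jaungo less likely. All of that stands for that scenario. The opposite pattern is also plausible, since Safety outcome measurements lists rash and pruritus as known reactions to Jaungo.

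**Exploratory status.** The Discussion calls the study preliminary and exploratory, which lowers the severity. The plan nevertheless states an efficacy hypothesis at α = 0.05, and the Discussion presents the study as critical for later confirmatory trials.

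**Conclusion.** The concern holds as a mismatch between stated rules. On the text available, LOCF has no planned on-treatment EASI to carry. Early leavers are excluded, given a change of 0, or represented by an unscheduled exit score. Because several exits can depend on outcome, the main analysis may not preserve the randomised comparison.

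The direction is not known in advance: losing placebo participants who worsen biases against Jaungo, and losing Jaungo participants with side effects or worsening biases toward it. The size cannot be fixed from the document. About 0.25 SD, or 0.55 of a standard error, is one illustration; it rests on assumed losses of 3 versus 1 of 12, normality, and loss of exactly the worst responders.

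The conclusion also assumes that Fig. 2 adds no interim or exit EASI. This should be fixed, but for an exploratory phase IIa trial it does not invalidate the design.

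**What to change.** 1. Define the main analysis set as all randomised participants in their assigned arm.
2. Take EASI and SCORAD at the planned week-3 time whether or not ointment was stopped or the case was closed early, where the participant agrees. This leaves the discontinuation and early-closure rules as they are.
3. For values still missing, replace LOCF with multiple imputation using arm, baseline EASI and any exit score. Imputation from arm and baseline alone cannot remove outcome-dependent loss, so step 2 and the sensitivity analysis must carry most of the correction.
4. Add a sensitivity analysis that assigns leavers no improvement or worse.
5. Report the present set as supportive, under a name that states its condition: randomised participants with a post-treatment outcome.

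The cost is revised analysis wording, a week-3 visit for a few early leavers, and slightly wider intervals. Some who withdraw consent will not return, so a few values will stay missing. Enrolment has begun, and a week-3 score that was not taken cannot be recovered later, so step 2 should come first.

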## Discussion

AD is an eczematous disorder that manifests with erythema, microvesiculation, exudation and crusting in its acute phase, and dry, red, scaly skin in its chronic phase [3]. Treatment guidelines for AD focus on the acute stage of the disease which includes emollients and topical GCs. Topical GCs are the mainstay treatment for AD flare-ups, and in many cases AD can be controlled with topical corticosteroids or topical calcineurin inhibitors; however, some chronic AD patients require other treatment options due to GC side effects.

*Jaungo* is an approved herbal ointment for xerosis cutis, frostbite, miliaria, anal fissures, and rhus dermatitis in Korea. Topical application of *Jaungo* was found to have anti-inflammatory and antiallergic activity in our previous in-vivo and in-vitro studies [5–7]. Based on these findings, we designed a phase IIa clinical study to determine the clinical efficacy of *Jaungo* and its possible treatment mechanism in chronic-stage AD. This preliminary and exploratory study is critical for future confirmatory clinical trials, as no information exists for *Jaungo*’s application dose, frequency, and length of time that it should be administered in AD.

One of the important issues that we had to consider in this study was the blindness between the experimental drug, *Jaungo*, and the placebo ointment. *Jaungo* has a unique color and aroma. The characteristic red color is due to the *Lithospermi* radix, and its distinctive aroma is due to the flavor components of bees wax and *Angelica gigantis* radix. Red iron oxide and ginseng-flavored extract were used to manufacture the placebo ointment. Substances, composition, and manufacturing methods of the placebo ointment were approved by the KFDA. Additionally, to conceal the distribution data from researchers and participants, a web-based random number generator system was developed by an independent expert on web programming using Django Web Framework.

Limitations of this study are that it involves only 34 participants in a single center. This could potentially influence the generalizability of the study results. However, this study was designed to find the most responsive AD symptoms, to establish the proper application dose and frequency of *Jaungo*, and to identify the possible mechanism of action utilized by *Jaungo* for further study. In conclusion, this exploratory study will contribute to establishing *Jaungo*’s efficacy, safety, and dose response in AD.

